## 8.2 AEFI(s) Evaluation Timeline

AEFI reporting will take place from the time the participant receives their first influenza vaccine until four weeks following the last vaccine administration.

Immediate AEFI(s) will be documented at the time of influenza vaccine administration. Delayed AEFI(s) will be checked one week after and up until the time point of the following vaccine administration four to six weeks later. Participants will be provided with a 7-day Side Effect Diary to facilitate documentation and recording of AEFIs (see Appendix II). Participants will be encouraged to report any AEFI(s) at any time during the study period.

## 8.3 Reporting and monitoring of AEFIs

### 8.3.1 Reporting responsibilities

Immunisation providers and medical practitioners in WA have a statutory requirement to notify AEFIs to the WA Department of Health through the WA Vaccine Safety Surveillance (WAVSS) System. The WAVSS reporting system is part of national reporting associated with the national network on Adverse Events Following Immunisation - Clinical Assessment Network (AEFI-CAN) (43).

Participants who receive their vaccine at the Stan Perron Immunisation Centre at PCH will be involved in automated surveillance with AusVaxSafety, a national vaccine safety initiative led by the National Centre of Immunisation Research and Surveillance (NCIRS) and funded by the Australian Department of Health.

Mild and moderate AEFIs do not require reporting to the WAVSS. These will be recorded, as well as any other AEFIs, by the study investigators as part of the Safety objectives evaluation.

A comprehensive list of AEFIs requiring reporting via the WAVSS System can be found in Appendix I. It includes the following entities:

- Abscess
- Acute flaccid paralysis
- Allergic reaction (generalised)
- Anaphylaxis
- Arthralgia
- Arthritis
- Brachial neuritis
- Death
- Encephalopathy
- Encephalitis
- Extensive limb swelling
- Fever >40.5 °C
- Guillain-Barré syndrome
- Hypotonic-hyporesponsive episode
- Injection site reaction (severe), including nodule
- Intussusception
- Lymphadenitis
- Meningitis
- Orchitis
- Osteitis
- Osteomyelitis
- Parotitis
- Severe and/or unusual rash
- Screaming
- Thrombocytopenia <50 x 10^9/L
- Toxic shock syndrome
- Vasovagal episode

### **8.3.2 Required reporting criteria**

The following information regarding AEFI(s) will be recorded by the study investigators:

- Event description
- Event grade
- Event duration
- Relationship to the influenza vaccine (related or unrelated event)
- Event expectedness (expected or unexpected event)
- Action taken by the Study investigator
- Required medical attention

### **8.3.3 Reporting Timelines**

All severe (non-mild, non-moderate) AEFIs will be reported within 48 hours. All serious AEFIs such as anaphylaxis, HHE and febrile convulsion will be reported within 24 hours of the event. Reports will be lodged via the WAVSS system as well as reported to the Data Safety Monitoring Board, to ensure participant safety.

#### **8.3.4 Data Safety Monitoring Board (DSMB)**

To ensure the safety of all study participants, a Data Safety Monitoring Board will be appointed. The DSMB will consist of five specialists from the following paediatric disciplines: Oncology, Haematology, Infectious diseases, Immunology and Neurology; as well as a Statistician.

The DSMB will receive a report issued by the study investigators every two weeks or at the completed recruitment of every 10 newly vaccinated study participants, regardless of the degree of possible AEs. In addition, the DSMB will receive a safety report after 6 participants have received the third dose of the vaccine in the 3 – <9 year age group and based on the safety outcomes of this report will provide a recommendation as to whether recruitment to the three dose schedule can commence in the 6-35 month age group.

Any unexpected, severe or serious AEFIs will be reported to the DSMB by the study investigators within the set timelines. The DSMB may recommend the study to be modified or terminated based on the reported events.

### **8.4 Stopping rules**

A stopping rule will be met under the following circumstances:

- Where two subjects receiving the influenza vaccine develop a severe or serious AEFI, or an unexpected AEFI that is similar in nature and cannot be attributable to any other cause.

Once the stopping rule has been applied, enrolment of participants will be paused until the outcome of investigations by DSMB has been issued.

Study conduct activities such ongoing data entry, laboratory evaluations and participants follow up will continue during the pause.

Enrolment and vaccination may proceed at the discretion of a minimum of three DSMB members.

If the stopping rule has been triggered by a serious AEFI in two subjects within the same age group (i.e. anaphylaxis in two children <9 years old), additional influenza vaccine will not be administered to further study participants after this time point.

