#### 8.1.4 Definition of a serious AEFI

A serious AEFI is an AE at least possibly related to the study vaccine that is:

- life-threatening
- requires inpatient hospitalization or prolongation of existing hospitalization\*
- results in persistent or significant disability/incapacity
- results in death

\* Serious AEFI in the case of hospitalization or prolongation of existing hospitalization for fever is defined as hospitalization or prolongation of existing hospitalization with fever >40.5 °C

Examples of serious AEFIs are:

1. **Anaphylaxis** - anaphylaxis following immunization has been reported, but generally occurs very rarely. In the case of influenza vaccine, these probably represent an allergic response to a residual component of the manufacturing process, most likely egg protein. Anaphylaxis to egg is not a contraindication to administration of the influenza vaccine. The only absolute contraindication to influenza vaccine is anaphylaxis after a previous dose of any influenza vaccine or any of the components of the influenza vaccine.
2. **Hypotonic-hyporesponsive episode (HHE)** - HHE is a sudden onset of pallor and cyanosis, muscle hypotonia and reduced responsiveness or unresponsiveness occurring after vaccination, where no other cause is evident such as a vasovagal episode or anaphylaxis. The episode usually

occurs 1 - 48 hours after vaccination and resolves spontaneously. There are no known long-term side effects of HHE.

3. **Febrile convulsion** - febrile convulsions are rare following immunisation. They do occur more commonly, but still at a low rate, after some vaccines. For example, MMR and MMRV vaccines are associated with an increased risk of febrile convulsions approximately 7 to 12 days after the 1st vaccine dose (40, 41).

In 2010, higher rates of fever and febrile convulsions occurred in children aged <5 years after influenza vaccination, especially in children aged <3 years. These were specifically associated with the vaccines Fluvax and Fluvax Junior at a rate of 4.4 per 1000 doses, compared with no such events reported among children who received an alternative vaccine in the same year (42). As a consequence, Fluvax and Fluvax Junior vaccines are no longer available in Australia.

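### Section 8.4 provides no automatic hold after a single death or other life-threatening AEFI at least possibly related to the vaccine, because both of its triggers need two affected children

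*Protocol*

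**What the plan says.** Section 8.4 has two event-driven triggers. The first is met "Where two subjects receiving the influenza vaccine develop a severe or serious AEFI", or when two develop unexpected AEFIs that resemble each other and have no other explanation. Its consequence is: "Once the stopping rule has been applied, enrolment of participants will be paused until the outcome of investigations by DSMB has been issued". The second ends the additional dose for further participants: "If the stopping rule has been triggered by a serious AEFI in two subjects within the same age group". Release is described as follows: "Enrolment and vaccination may proceed at the discretion of a minimum of three DSMB members".

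Section 8.1.4 defines the relevant class: "A serious AEFI is an AE at least possibly related to the study vaccine that is" life-threatening, fatal, disabling or a cause of hospitalisation. Section 8.3.3 sets the reporting time: "All serious AEFIs such as anaphylaxis, HHE and febrile convulsion will be reported within 24 hours of the event". These reports go to the state surveillance system and to the DSMB. Section 8.3.4 adds: "The DSMB may recommend the study to be modified or terminated based on the reported events". It also provides for a run-in review, in which "the DSMB will receive a safety report after 6 participants have received the third dose of the vaccine" in the group aged 3 to under 9 years, before children aged 6 to 35 months may enter the three-dose schedule.

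**The concern.** The additional dose is what the study adds to standard care: a second dose from age 9, and a third dose below it. Section 1.4 cites one previous three-dose study in children with cancer, small and more than 35 years old. Under a two-child threshold, the first related death or life-threatening event changes nothing automatically. Other immunosuppressed children could receive the non-standard dose while the DSMB is still considering that event.

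The wording of the pause is a second, smaller weakness. The children most exposed at that moment are already enrolled and waiting for their extra dose, yet the pause sentence mentions only enrolment. That vaccination stops too has to be inferred from the release sentence.

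**Working it through.** The protocol states no operating characteristic for the stopping rule, so there is no figure to reproduce. The finding rests on the text, and the arithmetic only gives a sense of scale.

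**Step 1. What each provision does after one related fatal or life-threatening event**

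| Provision | What sets it off | Effect after one event |
|---|---|---|
| 8.4, pause | Two subjects, severe or serious AEFI | None |
| 8.4, unexpected-AEFI limb | The same two subjects; resemblance also presupposes two cases | None |
| 8.4, end of additional dose | Two subjects in one age group, serious AEFI | None |
| 8.3.3, reporting | Any serious AEFI | Report within 24 hours; no hold ordered |
| 8.3.4, DSMB power | Reported events, no minimum number | Discretionary recommendation; no decision time given |
| 8.3.4, routine DSMB reports | Every two weeks or per 10 newly vaccinated children | Report only |
| 8.3.4, run-in review | Six third doses at 3 to under 9 years | Planned gate for ages 6 to 35 months only |
| 3.6 and 5.2, checks at each visit | That child's own condition | Does not respond to an event in another child |

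No row holds the extra dose automatically after a first event.

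**Step 2. How many extra doses could fall in the interval**

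Inputs from the protocol:
- 80 participants (3.7) over 24 months (3.8).
- Visits 4 to 6 weeks apart (5.2).
- First dose as soon as vaccine becomes available (6.1).

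Assumptions, because the protocol gives no figures:
- Two influenza seasons of equal size: 80 / 2 = 40 children per season.
- An even age split: 40 / 2 = 20 aged 9 or over and 20 younger.
- First doses given together at week 0.

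Timing of the extra dose:
- Age 9 and over, one interval after dose 1: weeks 4 to 6.
- Under 9, two intervals after dose 1: 2 × 4 = 8 to 2 × 6 = 12 weeks.

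Rates:
- Weeks 4 to 6: 20 / (6 − 4) = 10 per week, so 20 in two weeks.
- Weeks 6 to 8: none.
- Weeks 8 to 12: 20 / (12 − 8) = 5 per week, so 10 in two weeks. This is high if some are aged 6 to 35 months and still waiting for the run-in review.
- After week 12: none.

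If first doses were instead spread over 8 weeks, the extra doses would cover (12 − 4) + 8 = 16 weeks. The average would be 40 / 16 = 2.5 per week, or 5 in two weeks; this is an average and not a peak.

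The range is therefore from zero to about 10 in one week and 20 in two. A larger share of children aged 9 or over would raise the peak.

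**Step 3. Slack for a hold**

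The visit window allows 6 − 4 = 2 weeks at most, and none for a child already at week 6.

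**The case against.** The strongest reply is that this is a design choice and nothing in 8.4 is false or contradictory. A single serious event reaches the DSMB within a day, the DSMB's power to recommend a halt has no two-case minimum, and nothing obliges the investigators to go on dosing. All of that stands. A reader might infer that the protocol requires dosing to continue after a death, or leaves the DSMB powerless. The documents support neither; what is missing is only an automatic hold.

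A reader might also infer that the rule is certain to catch a second event, for example one death followed by one severe AEFI in another child. The text does not settle this. The words requiring similarity and the absence of another cause may qualify only the unexpected AEFI, or every event in the sentence. On the second reading that pair might not count.

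Section 8.4 illustrates its escalation with anaphylaxis in two children. Requiring two cases of treated anaphylaxis looks deliberate, so a pause after one would override an apparent choice. The fix leaves that choice alone.

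Two objections to a new trigger also have force. First, it could fire after a standard dose yet hold only the extra one. That is defensible because the standard doses are recommended care (1.2) and the additional dose is the part the study controls, but it remains a judgement. Second, 8.1.4 speaks of possible relation, whereas 8.1.2 and 8.3.2 record only related or unrelated. The wording of the trigger has to bridge this.

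**Conclusion.** The point holds in a narrow form. Both triggers in 8.4 need two children, so one death or other life-threatening AEFI at least possibly related to the vaccine produces a 24-hour report and a possible DSMB recommendation, with no hold on the extra dose in between. The pause sentence, read alone, covers enrolment only.

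No probability is attached. The protocol gives no rate for such events in this population, and the 4.4 per 1000 doses in 8.1.4 concerns febrile events with vaccines no longer available. The number of extra doses at risk in the interval is not fixed either. The figures of about 10 per week and 20 in two weeks rest on 40 children per season, an even age split and first doses given together. The number can be zero, depending on when the event falls. This is an optional improvement to a safety rule, and the confidence in it comes from the text rather than from these figures.

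**What to change.** Add one sentence to 8.4: any single AEFI meeting 8.1.4 that is fatal, or is life-threatening other than anaphylaxis that resolves with treatment, and that is not judged unrelated under 8.1.2, pauses enrolment and the study's additional doses in all age groups until at least three DSMB members release them. Standard-of-care doses continue unless the DSMB says otherwise. The two-subject rule stays as it is for all other events.

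The phrase about not being judged unrelated bridges the two causality scales. Naming the additional doses removes the need to infer a vaccination hold.

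The change is cheap: it reuses the 24-hour report and the existing three-member release, and needs no new visits, samples or staff. Its downside is an occasional short pause for an event later judged unrelated, which is plausible in children under treatment for cancer. Under the assumptions above, a hold at the busiest time would delay about 10 extra doses in one week and 20 in two. With at most two weeks of slack, some could fall outside the 4 to 6 week window, so a prompt DSMB decision matters.

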### **1.2 Current influenza vaccination schedule in children undergoing treatment for cancer**

Currently, all children in Australia aged 6 months to 18 years undergoing immunosuppressive therapy such as treatment for cancer are recommended to receive inactivated influenza vaccine as per The Australian Immunisation Handbook, 10th Edition (8). These recommendations have been developed by the Australian Technical Advisory Group on Immunisation (ATAGI) and approved by the National Health and Medical Research Council (NHMRC) (9, 10).

The recommendations are supported by a number of international studies, including one that was conducted locally in Perth in 2010 and 2011 by Kotecha *et al.*, which demonstrated that the inactivated influenza vaccine is safe, immunogenic and provides clinical protection in children receiving treatment for cancer (11-24). Kotecha *et al.* also demonstrated a significantly more effective immune response to two doses of the inactivated influenza vaccine in children <9 years of age compared to one dose. Therefore a recommendation was made that all immunocompromised children <9 years of age undergoing therapy for cancer should receive two doses of the inactivated influenza vaccine. Immunocompromised children aged ≥9 years continue to receive one dose of the inactivated influenza vaccine.

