### **3.5 Timing**

Participants must be enrolled before vaccination and sample collection begins. All eligibility criteria must be met and a consent form must be signed by the parent/guardian prior to entering the study.

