#### **FluQuadri**

For children aged  $\geq 3$  years  
Administration route: intramuscular injection  
Sponsor: Sanofi-Aventis Australia  
Quadrivalent inactivated influenza vaccine  
Each 0.5 mL pre-filled syringe contains:  
15  $\mu$ g hemagglutinin for each of the 4 recommended influenza virus strains  
 $\leq 100$   $\mu$ g formaldehyde

≤250 µg octoxinol 9

≤1 µg ovalbumin

Annual influenza vaccination is recommended before the influenza season starts. Influenza community circulation usually peaks between June and September in most parts of Australia. The influenza vaccine usually becomes available in March or April of each year.

If more than one influenza vaccine is recommended, these should be administered 4 weeks apart. The first vaccine should be administered as soon as it becomes available to ensure that there is enough time to receive the second (and third dose) before influenza circulation peaks.

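### Section 8.4 pauses only enrolment in one sentence and implies a vaccination hold in the next; the permanent stop can be misread; and the serious-AEFI threshold in 8.1.4 has no matching causality class

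*Protocol*

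**What the plan says.** After the trigger, Protocol section 8.4 makes four statements:

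- The pause: "Once the stopping rule has been applied, enrolment of participants will be paused until the outcome of investigations by DSMB has been issued".
- What carries on: "Study conduct activities such ongoing data entry, laboratory evaluations and participants follow up will continue during the pause".
- The restart: "Enrolment and vaccination may proceed at the discretion of a minimum of three DSMB members".
- The permanent stop: "If the stopping rule has been triggered by a serious AEFI in two subjects within the same age group", then "additional influenza vaccine will not be administered to further study participants after this time point".

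The trigger is two subjects with a severe or serious AEFI, or with similar unexpected AEFIs that have no other attributable cause.

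Section 8.1.4 confines serious AEFIs to events that are possibly related or more, and that meet one of four seriousness criteria. Section 8.1.2 defines two causality classes and 8.3.2 records the same two: related and unrelated. Expectedness is a separate axis. The severity grades in 8.1.1 carry no causality condition. Section 8.3.3 sets 48 hours for severe events and 24 hours for serious ones.

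**The concern.** These are operative safety instructions, so site staff should be able to follow them sentence by sentence. Three places do not allow that.

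1. The pause sentence and the restart sentence name different things. The dose under study is always given after enrolment, so a pause limited to enrolment would leave it untouched for every child already in the study.
2. The permanent stop refers to further participants. That may mean anyone still due the extra dose, or only children not yet enrolled.
3. The serious-AEFI definition uses a causal threshold that the recording scale cannot express. Seriousness is what drives the permanent stop and the 24-hour report, so an event without a class has no settled consequence under either.

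**Working it through.** The protocol gives no figure to reproduce here. The check sets the provisions side by side, with a little arithmetic on visit timing.

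**Step 1: the pause against its neighbours (8.4).**

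| Sentence | Enrolment | Vaccination |
|---|---|---|
| Pause | stopped | not mentioned |
| Continuing activities | not listed | not listed |
| Restart | at DSMB discretion | at DSMB discretion |

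Vaccination needs DSMB agreement to proceed but was never expressly stopped. The second and third rows imply that it was.

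**Step 2: can an enrolled child fall due during a pause?** Section 3.5 states: "Participants must be enrolled before vaccination and sample collection begins". Every dose therefore follows enrolment. Section 5.2 spaces visits 4 to 6 weeks apart, and section 1.2 gives the standard schedule as one dose at 9 years and over and two doses below 9.

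- Last standard dose to extra dose, both groups: one interval, 4 to 6 weeks.
- Dose 1 to extra dose, 9 years and over: 1 × (4 to 6) = 4 to 6 weeks.
- Dose 1 to extra dose, under 9: 2 × (4 to 6) = 8 to 12 weeks.
- For a child *t* weeks past the last standard dose at the trigger, the window closes in 6 − *t* weeks, so within 6 weeks at most.
- A dose due at week 4 and held has 6 − 4 = 2 weeks before it passes the visit maximum.

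So enrolled children can fall due for the extra dose while a pause is in force, and the wording of the pause matters to them.

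**Step 3: the permanent stop (8.4).** The sentence bars administration from a point in time, which favours reading it as covering everyone still awaiting the extra dose. The word further allows the narrower reading. Take an enrolled 5-year-old awaiting dose 3 after two anaphylaxis cases under 9: the first reading covers this child and the second does not.

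**Step 4: the causality classes (8.1.2).** Related needs plausible timing and no ready explanation from the child's condition, another illness or other treatment. Unrelated needs evidence of a different cause, implausible timing, or both.

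| Timing plausible | Readily explained otherwise | Evidence of other cause | Class |
|---|---|---|---|
| No | either | either | Unrelated |
| Yes | No | No | Related |
| Yes | Yes | Yes | Unrelated |
| Yes | Yes | No | Neither |

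The last row is the gap. A child on chemotherapy with a well-timed event that the chemotherapy could readily explain, but with nothing to show that it did, belongs there. Such an event is arguably possibly related under 8.1.4, but 8.3.2 has no entry for it.

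**Step 5: what follows for a last-row event that meets a seriousness criterion.**

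- If also severe: reported to the DSMB within 48 hours (8.3.3) and counted toward the pause (8.4).
- If unexpected: also reportable to the DSMB (8.3.4).
- If neither: it reaches the DSMB through the regular report, issued every two weeks or at every 10 newly vaccinated participants (8.3.4).
- In all cases: undetermined for the 24-hour report and for the permanent stop.

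**The case against.** The strongest reply is that 8.4 should be read whole. If vaccination may proceed only at the DSMB's discretion, it does not proceed by default, and it is not listed among the continuing activities. This stands. A reader might infer that the protocol lets extra doses go on during a safety pause; it does not say so, and the section as a whole points the other way. What remains is an inconsistency between sentences.

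On the permanent stop, the natural reading is that nobody receives the extra dose from that point. This also largely stands; the wording can be misread but need not be. A reader might further infer that the age scope is undefined, because the trigger is specific to an age group and the action is not. The documents do not support that. As worded, the action applies to all ages, which is a legitimate conservative choice.

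On causality, 8.1.2 presents itself as general guidance for investigator judgement, and severe events reach the DSMB regardless. Both points stand and limit the consequence. A reader might also infer that any unexplained event after vaccination escapes classification. It does not: with plausible timing and no cause found, it is most naturally not readily explained, and so related. The gap is confined to events with a ready but unproven alternative explanation.

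Finally, one might want standard doses to continue by default during a pause. Section 1.2 reports the recommendation that "all immunocompromised children <9 years of age undergoing therapy for cancer should receive two doses of the inactivated influenza vaccine", and section 6.1 wants the first dose given early so that "there is enough time to receive the second (and third dose) before influenza circulation peaks". Against this, the trigger counts subjects after any dose of the vaccine and the restart sentence covers vaccination generally. The documents do not settle that trade-off, so it belongs with the DSMB.

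**Conclusion.** The point holds as a minor correction to safety wording. Section 8.4 is internally inconsistent on whether vaccination is paused, its permanent stop can be misread as applying to new enrolees only, and 8.1.4 uses a causal threshold that 8.1.2 and 8.3.2 cannot record.

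The practical effect is bounded. For a severe event in the causality gap, what is left open is 24 versus 48 hours and whether the event counts toward the permanent stop. No endpoint, sample size or analysis is affected. The protocol gives no event rate, so nothing is claimed about how often the rule would fire.

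This rests on two readings: that the restart sentence reflects the intended scope of the pause, and that the no-other-cause condition in the trigger attaches only to unexpected AEFIs, so that severe events count whatever their cause.

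**What to change.** 1. **Section 8.4, pause.** Amend to: *enrolment and administration of the additional study dose to enrolled participants will be paused until the DSMB outcome has been issued*. Leave the handling of standard-schedule doses during a pause to the DSMB.
2. **Section 8.4, permanent stop.** Replace the reference to further participants with: *any participant, enrolled or new, who has not yet received the additional dose*.
3. **Section 8.1.4.** Define a serious AEFI as a qualifying event not judged unrelated. Alternatively, add a possibly related class to 8.1.2 and 8.3.2, which means one more option on the adverse event form.

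The cost is a few sentences. Some extra doses may slip past the 6-week visit maximum (a dose due at week 4 does so after a hold of more than 2 weeks), though the whole-section reading of 8.4 already implies this. Slightly more events will count as serious.
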